### Intervention fidelity and safety secondary outcomes

Intervention fidelity measures will be undertaken to understand the degree to which the intervention was able to be delivered as planned. These include: provision of oral nutrition supplements and consumption, PERT recommendations, medication recommendations, referrals to support services, feeding tube insertions, and feeding tube complications.

### Economic evaluation

Economic measures will be used to inform an economic evaluation, including both costs and measures of utility necessary to undertake a cost utility analysis. Health utility will be measured using the EQ-5D-5 L, which is a generic measure of health-related quality of life that does not include the cancer symptom-specific domains of the EORTC QLQ-C30 [43, 44]. However, use of a generic health utility scale is necessary for calculating the Quality-Adjusted Life Years (QALYs) lived necessary for conducting an economic evaluation consistent with welfare economics theorem. Other measures include; home care service provision (paid and unpaid) using the iMTA MCQ, direct health costs captured using Medicare Benefits Schedule (MBS) and Pharmaceutical Benefits Scheme (PBS) data, direct costs associated with hospital admissions, days spent in hospital, procedures performed in hospital, subjective reports on additional non-MBS health service use, e.g. private dietitian, and costs associated with feeding tube insertions and complications [53]. An incremental cost-utility analysis will be undertaken from the societal (primary), health service (secondary) and patient (secondary) perspectives. Costs will be valued at a 2024 base-year. QALYs lived will be calculated using an Australian utility value set for the EQ-5D-5 L [54]. Bootstrap resampling will be used to calculate a 95% confidence ellipse and cost-effectiveness acceptability curves.

### Power calculation

A two-group comparison power analysis using the primary outcome, a power of 80%, and two-tailed alpha of 0.05 was undertaken. We considered that the minimum standardised effect that would be needed to justify the cost of the intervention would be a delta of 0.50 (large effect). In absolute terms, this is a change of 0.15 in health utility (scale value of 1 = perfect health, value of zero = death) given a standard deviation in our TEND study data of 0.29 for health utility at baseline [7]. With these inputs and considering inclusion of a baseline measurement and two follow-up measurements (3 months and 6 months) with correlation between them of 0.41 (based on data from our previous randomised controlled trial) in the model, we calculated that we would need *n* = 34 participants per group. We increased this requirement by 20% to *n* = 41 per group to account for potential loss to follow-up or missing data.

### Blinded outcomes

The primary outcome measure (QoL) will be collected and analysed by blinded research staff. The baseline QoL survey will be completed prior to group allocation and then at three- and six-months via REDCap. If the participant choses to do this in person, the survey will be completed by alternating research assistants, to ensure this measure remains blinded. In the event the study group is revealed to the research assistant, the survey will be ceased, and another blinded research team member will complete the survey with the participant.

### Database extraction

The intervention dietitians will have access to each hospital’s EMR to allow for data collection and collaboration with multi-disciplinary members to occur. Data extractions from MBS and PBS databases will be completed at the end of the trial where possible.

### Data analysis

#### Primary and secondary trial outcomes

Analyses will be undertaken on an intention-to-treat basis. The primary outcome (EORTC QLQ-C30 summary score) will be compared between groups using a linear mixed model analysis approach, using values collected at three and six months, and adjusting for baseline values of this variable as well as age, sex, cancer stage, and malnutrition risk score (PG-SGA_SF_ score) [29, 43]. Group allocation will be treated as a fixed effect, while individual participants and assessment time points will be treated as random effects. We will conduct relevant checks of distributional assumptions and model fit. Twelve-month mortality will be compared between groups using Cox proportional hazards regression analysis, adjusting for baseline values of health-related quality of life (EORTC QLQ-C30 summary score), as well as age, sex, cancer stage, and malnutrition risk score (PG-SGA_SF_ score) [29, 43]. Multiple imputation will be used in the event of missing data with checking or relevant assumptions for missing-ness to inform the final imputation approach [55].

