### Participants and setting

This study will recruit patients with newly diagnosed borderline resectable, locally advanced or metastatic pancreatic cancer who will be receiving or have already received one cycle of chemotherapy treatment across Victorian health care services. Regional and rural health care services are included in participating sites to help reduce inequities across cancer care as demonstrated in the Australian Cancer Plan [24].

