### Randomisation and blinding

The random allocation sequence will be developed by a statistician who has no role in the recruitment of participants or data collection. Dynamic randomisation methods will be employed using STATA 18, based upon dichotomisation of malnutrition risk score at baseline assessment (Patient Generated Subjective Global Assessment Short Form (PG-SGA_SF_) score of < 12 vs. ≥ 12 based on distribution of baseline scores from our previous research) cancer stage (borderline resectable or locally advanced vs. metastatic), and commencement of chemotherapy (yes vs. no) [7, 28, 29]. The randomisation sequence will be generated by the study project managers and kept in a password-encrypted file. The project managers will contact the intervention dietitian and provide the sequential participant registration number. Participants will be informed of their group allocation via phone by the intervention dietitian.

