### ‘Usual care’ control group

Routine dietetic care will be received by those participants randomised to the control group, also known as usual nutrition care. Usual care most commonly involves nurse-led malnutrition screening at each chemotherapy visit or acute inpatient admission, with patients at risk of malnutrition referred to a dietitian for nutrition assessment and intervention to optimise nutrition status. The timing and delivery of usual care will differ between health services.

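### Commencement of chemotherapy is balanced by the randomisation but is a covariate in neither the primary mixed model nor the Cox model; adding it is a free, modest improvement

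*Protocol article*

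**What the plan says.** In the Protocol article, *Randomisation and blinding* names three allocation factors. The first is malnutrition risk: "Dynamic randomisation methods will be employed using STATA 18, based upon dichotomisation of malnutrition risk score at baseline assessment", with PG-SGA SF cut at 12. The second and third are "cancer stage (borderline resectable or locally advanced vs. metastatic), and commencement of chemotherapy (yes vs. no").

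*Participants and setting* shows that the third factor varies between participants. The trial enrols patients "who will be receiving or have already received one cycle of chemotherapy treatment".

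*Primary and secondary trial outcomes* then fixes the covariates. The mixed model for the QLQ-C30 summary score at three and six months is fitted "adjusting for baseline values of this variable as well as age, sex, cancer stage, and malnutrition risk score" (PG-SGA SF). For survival, "Twelve-month mortality will be compared between groups using Cox proportional hazards regression analysis, adjusting for baseline values of health-related quality of life", followed by the same age, sex, cancer stage and PG-SGA SF terms.

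Both lists therefore hold two of the three allocation factors, plus age and sex, which are not allocation factors. Chemotherapy commencement appears in neither list, and the article gives no reason.

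**The concern.** When allocation is forced to balance on a factor that predicts the outcome, that factor contributes almost nothing to the chance difference between the groups. A linear model without the factor still counts its variance as residual noise. The reported standard error then exceeds the true one, the confidence interval is wider than it need be, and the test rejects less often than its nominal level. The usual remedy is to analyse by the factors used to randomise.

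The factor could plausibly matter. The summary score includes fatigue, nausea and vomiting, appetite loss and diarrhoea, and the sponsor chose chemotherapy status as one of only three balancing factors. At stake is some precision in a trial planned on 34 evaluable participants per group. The validity of the comparison is not in question.

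**Working it through.** **Inputs from the documents** (*Power calculation*): "a power of 80%, and two-tailed alpha of 0.05 was undertaken"; standardised effect 0.50; one baseline and two follow-up measurements with correlation ρ = 0.41; 34 per group, raised by 20% to 41.

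**Reproducing the plan's figure.** For an analysis of the mean of two follow-ups adjusted for baseline, the variance factor is (1 + ρ)/2 − ρ² = 0.705 − 0.1681 = 0.5369. Without this factor, n per group = 2(1.960 + 0.842)²/0.50² = 62.79. Then 62.79 × 0.5369 = 33.7, so 34 per group, and 34 × 1.2 = 40.8, so 41. Both stated figures reproduce, and neither takes any credit for chemotherapy status.

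**Effect of the omission in the mixed model.** In SD units, the model standard error at 34 per group is √0.5369 × √(2/34) = 0.1777. Let R² be the share of residual variance that chemotherapy status explains after the listed covariates, and take allocation to be balanced on it. Then:

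- true SE = 0.1777 × √(1 − R²), so the model SE is too large by the factor 1/√(1 − R²);
- true type I error without the factor = 2[1 − Φ(1.96/√(1 − R²))];
- power without the factor = Φ[(0.50 − 1.96 × 0.1777)/true SE];
- power with the factor = Φ[0.50/true SE − 1.96].

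The documents give no R², so a range is assumed:

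| Assumed R² | SE too large by | True alpha, factor omitted | Power, omitted | Power, included | Points forgone |
|---|---|---|---|---|---|
| 0 | 0% | 5.0% | 80.3% | 80.3% | 0 |
| 0.02 | 1.0% | 4.8% | 80.6% | 81.1% | 0.5 |
| 0.05 | 2.6% | 4.4% | 80.9% | 82.3% | 1.4 |
| 0.10 | 5.4% | 3.9% | 81.6% | 84.3% | 2.7 |

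**Simulation check.** Biased-coin minimisation on three binary factors was simulated (assumed probability 0.8, prevalence 50% each), with a baseline-adjusted analysis of 68 participants. At R² = 0.10 the model SE without the factor was 0.179, against an empirical SE of about 0.17. Type I error was 4.1% without the factor and 5.0% with it; power was 79.4% and 82.5%. Simulated power is about two points below the formula even at R² = 0 (78% against 80.3%), so the comparison should be made within the simulation. There, power without the factor does not fall as R² rises from 0 to 0.10.

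**Cox model.** The linear formula does not carry over, so this was simulated: 82 participants, assumed control twelve-month mortality of about 50%, assumed treatment hazard ratio 0.5, 2,000 runs per setting.

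| Assumed hazard ratio of the factor | Mean log HR, omitted / included | SE, omitted / included | Power, omitted / included |
|---|---|---|---|
| 1.5 | −0.72 / −0.73 | 0.372 / 0.373 | 49% / 50% |
| 2 | −0.72 / −0.74 | 0.370 / 0.372 | 50% / 52% |
| 3 | −0.67 / −0.73 | 0.362 / 0.366 | 46% / 52% |

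Without the factor the standard error is slightly smaller. Power is lost because the estimated log hazard ratio moves toward zero. With 2,000 runs the simulation error on a power near 50% is √(0.25/2000) = 1.1 points, so only the largest difference deserves weight.

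**The case against.** The strongest reply is that the residual effect may be close to nil. Eligibility confines the contrast to patients who have not yet started and patients who have had one cycle, and those who decline or are unsuitable for chemotherapy are excluded. The outcome is measured at three and six months, well after a first cycle. The baseline survey precedes allocation, and both models adjust for that score and for PG-SGA SF, which should absorb part of any first-cycle effect. All of this stands. It is why the range starts at R² = 0, where nothing is lost.

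A second reply is that an article condenses, and covariates can be settled in an analysis plan. That does not answer the point. The article gives an explicit covariate list for each model, and both lists leave out the same allocation factor.

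Four stronger readings are tempting, and the documents do not support them:

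- *The trial falls below its planned 80% power.* This would require the sample size to have assumed adjustment for chemotherapy status. It did not: 34 per group follows from the effect size, the correlation and the measurement schedule alone.
- *Standard errors are inflated in the Cox model too.* In that model the omission attenuates the log hazard ratio and leaves the standard error slightly smaller.
- *The primary comparison is biased or has excess false positives.* The linear treatment estimate is not biased by the omission, and any error in the test is on the conservative side.
- *Site must be in the models as well.* The *‘Usual care’ control group* section does say that "The timing and delivery of usual care will differ between health services". But site is not an allocation factor, so the argument from balancing and then ignoring a factor does not reach it. Whether to model site is a separate choice.

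**Conclusion.** The mismatch is real: one of three allocation factors is missing from both models, while the other two are present in both. Its consequence is conditional and modest. If chemotherapy status is prognostic beyond the listed covariates, the primary test is slightly conservative and some attainable power is given up, at most about three points over the range examined. If it is not prognostic, there is no cost either way. For mortality, the consequence is an attenuated hazard ratio, noticeable only if the factor is strongly prognostic.

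These sizes rest on assumptions that the documents do not supply: the R² range, near-perfect balance under the allocation method, 50% factor prevalence, the factor's hazard ratio, control mortality and the treatment hazard ratio. The mismatch itself depends on none of them. This is a free improvement to the plan; it does not correct an error that threatens the trial's conclusion.

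**What to change.** Add one sentence to *Primary and secondary trial outcomes*, for example: *Both the mixed model and the Cox model will also include, as a fixed covariate, chemotherapy status at randomisation (started or not started), as recorded for allocation.* If the sponsor prefers to leave the factor out, the protocol should give the reason.

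The cost is one degree of freedom in each model. The sample size does not change and nothing new has to be collected, because the allocation procedure needs this variable for every participant. The Cox hazard ratio becomes conditional on one further factor, which should be noted when it is reported. The change should be made before any outcome data by group are seen, so that it cannot be read as a choice made after the fact.

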#### Mediation analysis

Mediation analysis is increasingly used in randomised controlled trials to confirm the hypothesised working mechanism underlying an intervention. We will use path analysis techniques and follow four recommended steps [56]; (i) descriptive statistics, (ii) test of direct effect of treatment on the mediator (iii) testing the indirect (mediating) pathway, and (iv) testing the indirect (mediating) pathway for potential confounding. Both mechanistic and intervention fidelity and safety secondary outcomes will be included in these mediation analyses.

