**Methods:**

This multicentre randomised controlled trial will recruit adults newly diagnosed with borderline resectable, locally advanced or metastatic pancreatic cancer from multiple health services across Victoria (metropolitan and regional). The control group will receive usual nutrition care, which is site-dependent. The intervention group will receive weekly telehealth dietetic consultations for six months, targeting nutritional adequacy through dietary education and counselling, oral nutrition supplement drinks and dietetics-led symptom management advocacy, including appropriate dosing of pancreatic enzymes. Escalation to supplemental jejunal tube feeding may occur if clinically required in the intervention arm. The primary outcome is quality of life (EORTC-QLQ C30 summary score); secondary outcomes include survival, chemotherapy dosing changes, and nutrition status markers including body composition. Outcomes will be measured at baseline, and three- and six-months.

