#### Enteral feeding

The intervention dietitian will utilise evidence-based guidelines from the European Society for Medical Oncology (ESMO) and European Society for Clinical Nutrition and Metabolism (ESPEN) to determine when escalation to enteral nutrition is required [35, 36]. The ESMO guideline for UGI cancers include considering enteral nutrition to maintain nutrition status when oral feeding (including the use of oral nutrition supplement drinks) is predicted to remain suboptimal [35]. The ESPEN guidelines recommend commencing enteral nutrition when there is suboptimal oral intake of less than 60% of estimated energy expenditure for greater than ten days, where the goal of EN would be to supplement oral intake to meet nutrition requirements [36]. Participants will be assessed for the need of a feeding tube at each dietitian consult and if deemed appropriate by the intervention dietitian, escalation to enteral nutrition will be discussed with the participant. Some participants may require a tube insertion at the commencement of the intervention due to previous substantial weight loss or deteriorating nutrition status. Participants are educated on their first assessment that they may also request this to occur prophylactically. If the participant agrees to an enteral feeding tube insertion, the participant’s primary health service gastroenterology team will be notified by the intervention dietitian to facilitate insertion. If a patient has a borderline resectable tumour, the treating surgeon will be consulted to ensure that tube insertion doesn’t interfere with the participant’s planned surgery. Participants will be supplied with the enteral formula; Abbott Vital^®^ 1.5 cal/mL, a peptide-based, partially hydrolysed, nutritionally complete formula [37]. Alternative formulations may be required as per the dietitian’s recommendation in consultation with the patient. As soon as practical after the feeding tube has been inserted a Home Care Nurse (healthcare company representative) will visit the participant (and/or their family and carers) at home or at their healthcare institution to provide training and education on using and caring for the feeding tube.

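### Several planned mediators are acts of delivering the intervention or follow clinical deterioration, so the mediation analysis cannot confirm a mechanism through them

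*Protocol article*

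**What the plan says.** The Mediation analysis section gives the purpose as confirming the intervention's hypothesised working mechanism. It plans path analysis in four steps: (i) description, (ii) the effect of treatment on the mediator, (iii) the indirect path, and (iv) a test of that path for confounding. It then commits to the mediators: "Both mechanistic and intervention fidelity and safety secondary outcomes will be included in these mediation analyses".

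The section on intervention fidelity and safety outcomes says that the fidelity measures are there to show "the degree to which the intervention was able to be delivered as planned". It lists "provision of oral nutrition supplements and consumption, PERT recommendations, medication recommendations, referrals to support services, feeding tube insertions, and feeding tube complications".

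On who receives a tube, the abstract says "Escalation to supplemental jejunal tube feeding may occur if clinically required in the intervention arm". The Enteral feeding section cites a guideline trigger of "suboptimal oral intake of less than 60% of estimated energy expenditure for greater than ten days" and adds: "Some participants may require a tube insertion at the commencement of the intervention due to previous substantial weight loss or deteriorating nutrition status". It also lets participants ask for a tube prophylactically. Under Pharmacological support, the need for PERT is assessed from symptoms and weight loss, and its timing and dosage are guided by intake and symptoms.

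For controls, usual care includes screening, "with patients at risk of malnutrition referred to a dietitian for nutrition assessment and intervention to optimise nutrition status".

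**The concern.** A mediation analysis supports a mechanism only if two paths carry information. Treatment must change something that is not simply the treatment itself, and the link from that variable to the outcome must be free of common causes, or adjusted for them. The listed fidelity and safety measures strain both conditions. Some record what the study dietitian did, so a difference between arms shows that the intervention was delivered and says nothing about how it works. Others, tubes above all, are given because a participant is doing badly, and doing badly plausibly lowers quality of life in its own right.

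At stake is the reading of a secondary analysis. The trial could report that tube feeding or PERT advice lowers quality of life, or that the benefit bypasses them, when the pattern only reflects who was selected to receive them. Tube feeding and enzyme dosing are components that the trial sets out to evaluate as part of its package.

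**Working it through.** **Step 1. Sort the listed measures by what they can show.**

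| Measure | What it records | Consequence in the path model |
|---|---|---|
| Provision of study supplements; study-dietitian PERT and medication recommendations | Delivery of the assigned intervention | Step (ii) largely restates allocation |
| Tube complications | Events possible only in someone with a tube | Carries little beyond tube insertion itself |
| Tube insertion | Response to poor intake, weight loss or deteriorating nutrition status; sometimes prophylactic on request | Path to quality of life open to confounding by indication |
| Supplement consumption; referrals | Behaviour or care that can also occur under usual care | Usable only if recorded alike in both arms |

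PERT advice sits in two rows: it is an act of delivery, and it also follows symptoms.

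**Step 2. Ask whether step (iv) can deal with the confounding.** The drivers of tube and PERT decisions are intake and symptoms as they change from week to week. The Nutrition optimisation section describes intake assessment by the intervention dietitian at each review. The Nutrition impact symptoms section describes recording at each consult for intervention participants. For controls, the Data collection section describes outcome data at baseline, three and six months, and no weekly record. A test for confounding cannot adjust for a time-varying driver that is described for only one arm.

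**Step 3. The protocol's own figures.** It gives no figure for the mediation analysis. The sample size matters here only because it sets the size of the illustration. With d = 0.50, r = 0.41, one baseline and two follow-ups:

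n = 2(1.960 + 0.842)²/0.50² × [(1 + 0.41)/2 − 0.41²] = 62.79 × 0.5369 = 33.7, so 34 per group; 34 × 1.2 = 40.8, so 41. The stated figures reproduce.

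**Step 4. Illustration of size.** The inputs are assumptions, except for 41 per arm and a total effect of 0.50 SD, which come from the Power calculation section.

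- Severity U is standard normal and unmeasured. In the intervention arm, P(tube) = 1/(1 + exp(1.1 − 1.2U)), about 30% on average.
- Control tube use is 0, 20% or 50% of that rate.
- Quality of life has within-arm SD 1 and correlation 0, −0.3 or −0.5 with U. The tube has no true effect.
- Indirect effect = (difference in tube rate) × (tube coefficient from a regression on arm and tube). There were 4000 runs per scenario.

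| Control rate relative to intervention | Correlation of U with QoL | Treatment-to-tube path | Indirect effect (truth 0) | Direct effect (truth 0.50) | Tube coefficient falsely significant |
|---|---|---|---|---|---|
| 0 | 0 | 0.295 | 0.002 | 0.500 | 5.4% |
| 0 | −0.3 | 0.297 | −0.085 | 0.584 | 14.1% |
| 0 | −0.5 | 0.297 | −0.146 | 0.645 | 30.0% |
| 20% | 0 | 0.238 | 0.002 | 0.498 | 5.5% |
| 20% | −0.3 | 0.239 | −0.068 | 0.569 | 15.4% |
| 20% | −0.5 | 0.238 | −0.107 | 0.607 | 31.9% |
| 50% | 0 | 0.147 | 0.001 | 0.497 | 4.8% |
| 50% | −0.3 | 0.146 | −0.040 | 0.546 | 17.3% |
| 50% | −0.5 | 0.147 | −0.065 | 0.568 | 38.5% |

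Two things follow. Without confounding by severity there is no bias, even when no control has a tube. With it, bias remains when controls also receive tubes. The indirect effect shrinks because the difference in tube rates shrinks, but the false-positive rate for the tube coefficient does not fall.

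**The case against.** **Controls may have these items too.** A reader might infer that the fidelity and safety outcomes exist only in the intervention arm. The article does not say so. Controls can be referred to a dietitian for intervention. The Pharmacological support section refers to prescriptions for all participants, although it sits under the Intervention group heading. Tube insertion and complication costs enter the economic evaluation, and EMR and PBS data may cover both arms. This stands: how these items are recorded in controls is unclear, and the point does not rest on their being absent.

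**Tubes are not near-collinear with allocation.** A reader might infer that they are. At an assumed 30% against 0%, r = 0.5 × 0.30/√(0.15 × 0.85) = 0.42, and the variance inflation is 1/(1 − 0.42²) = 1.2. This stands.

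**The wrong sign is not assured.** A reader might also infer that the indirect effect must point to harm. Tubes may be prophylactic, and those placed at the start because of earlier weight loss reflect baseline severity, for which stage and PG-SGA SF are available. This stands in part: baseline adjustment helps with early tubes but not with tubes prompted by later decline.

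**Step (iv) plans a confounding check, and every mediator faces this problem.** Both are true. Step (iv) can flag confounding by measured variables but cannot remove what is unmeasured. Weight or PG-SGA SF as mediators are also not immune, but they are outcomes measured in both arms, not treatment decisions prompted by deterioration.

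**This is detail for the analysis plan.** Confounder sets and model form are. The choice to include these outcomes is not: the article states it outright, and an analysis plan that follows it inherits the problem.

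**Conclusion.** The point holds in a limited form. The protocol commits to mediators that include acts of delivery, for which step (ii) cannot confirm a mechanism, and tube complications, which presuppose a tube. It also commits to tube insertion and PERT advice, whose path to quality of life is open to confounding by indication that step (iv) cannot remove.

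Under the assumed inputs, the spurious indirect effect through tubes ranges from about −0.04 to −0.15 SD, against a design effect of 0.50 SD. The direct effect is overstated by a similar amount. These figures depend on the assumed tube rate, on the strength of unmeasured severity and on no adjustment for it; with no such severity the bias is nil. The documents do not fix its size or sign. The bias comes from indication and not from a mediator occurring in one arm.

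The mediation analysis is secondary. The primary comparison is not affected, but what may be concluded about mechanism is.

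**What to change.** Change the Mediation analysis section as follows.

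- **Mediators:** restrict them to variables collected the same way in both arms at three months: weight, PG-SGA SF, muscle ultrasound, calf circumference and grip strength. CT muscle mass is planned only at baseline and six months, so it cannot precede the outcome. Include RDI only if it is taken from the EMR in both arms, because the article also allows its collection at the weekly dietitian consultations.
- **Outcome and adjustment:** use the six-month QLQ-C30 summary score, so that mediator precedes outcome, and adjust for the baseline mediator, baseline quality of life, stage and PG-SGA SF.
- **Delivery-only and tube-complication measures:** take them out of the path models and report them descriptively.
- **PERT, supplement or tube use:** keep as a mediator only if extracted comparably from EMR or PBS records in both arms, and interpret it with a sensitivity analysis for unmeasured mediator-outcome confounding.

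The cost is revised wording, fewer mediation models, and some extraction effort if PERT, supplement or tube use is kept. Residual mediator-outcome confounding is reduced, not abolished.
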